#### Subgroup Analysis

Subgroup analyses will be performed to determine if there are any trends, similarities, or differences in the mean outcomes of the 4 NDD diagnostic groups (ADHD, ASD, CP, and FASD); the CP and FASD groups are likely to have relatively fewer participants than the ADHD and ASD groups due to their lower prevalence.

#### Sensitivity Analysis

Sensitivity analysis will test variations in assumptions regarding estimated costs and reported health care usage. With the retail cost of the intervention under discussion, a range of prices will be explored based on the HWTP data, and the corresponding ICERs will be calculated. Parameter uncertainties associated with TU will be explored through scenario analyses, incorporating the 95% CI of mean estimates.

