### Sample Size Calculation

The BNBD-NDD RCT was powered to detect a group by time interaction across the 3 data collection time points (baseline, 4-month, and 8-month) and between the BNBD-NDD and usual care groups. The primary sleep outcome was the Disorders of Initiating and Maintaining Sleep (DIMS) [22] variable. To achieve a power of 0.80 with an α of .05, 39 participants per group would have to complete the DIMS measure at 8 months. Based on this analysis and the anticipated postenrollment dropout rate of 50% from a previous BNBD RCT, an estimated 160 participants were targeted for enrollment at baseline.

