### Randomization and Blinding

Participants were randomized using a block stratified approach with 1:1 allocation to either the intervention (BNBD-NDD) or the usual care group and were not blinded to their assigned group. Stratification was by parent-reported primary NDD diagnosis.

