#### Reference Case CEA

In the reference case analysis using the family payer perspective, the ratio of the difference in mean cost between groups to the difference in mean PedsQL total score per group will be used to estimate the ICER. An ICER will be calculated from the family’s perspective.

ICER = Costs_(BNBD-NDD + usual care)_ − Costs_(usual care)_ / Effect_(BNBD-NDD + usual care)_ − Effect_(usual care)_

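### The sensitivity analysis varies only price, costs and service use, so the reported ICERs carry no sampling uncertainty from the PedsQL difference or from its joint distribution with cost

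*Protocol article*

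**What the plan says.** Protocol article, Reference Case CEA: the difference in mean cost between groups over the difference in mean PedsQL total score "will be used to estimate the ICER", from the family payer's perspective.

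Sensitivity Analysis: "Sensitivity analysis will test variations in assumptions regarding estimated costs and reported health care usage". A range of retail prices drawn from the willingness-to-pay responses is then put through the ICER. For service use, "Parameter uncertainties associated with TU will be explored through scenario analyses, incorporating the 95% CI of mean estimates". Every source of uncertainty named in that section belongs to the numerator.

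Data Analysis, Overview: regressions of the efficacy measures on baseline characteristics will report the mean group difference with its variance, P value and R². Neither this section nor the CEA section says that this variance enters the ICER.

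Sample Size Calculation: "The primary sleep outcome was the Disorders of Initiating and Maintaining Sleep (DIMS"), so the trial was not sized on PedsQL. The requirement is that "39 participants per group would have to complete the DIMS measure at 8 months".

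**The concern.** An ICER is a ratio of two estimated differences, and both have sampling error. A set of ICERs obtained by changing price and TU while holding the PedsQL difference at its point estimate shows how the ratio responds to cost assumptions. It does not show how well the data determine the ratio. The omission may matter more here than usual: the BNBD-NDD Cost section makes the family's direct cost mainly the retail price, and once a price is chosen that component is the same for every intervention family.

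Two consequences follow. First, the scenarios would give a finite set of ICERs even if the data could not exclude a zero or negative effect on quality of life. Second, when the effect interval includes zero the ratio is hard to read, because a negative ICER can mean either that the programme is cheaper and better or that it is dearer and worse. The abstract and Discussion make their case for the programme conditional on its being cost-effective, and the Discussion foresees use in public funding decisions.

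**Working it through.** **The plan's own figure.** 39 completers per group is 78 in total. With 50% dropout, 78 / (1 − 0.5) = 156, against the stated 160 (80 per arm, so 40 completers per arm). The enrolment target is reproduced apart from rounding. The 39 itself cannot be reproduced, because no DIMS effect size, SD or correlation is given. As a marker only, a simple two-sided comparison of two means at power 0.80 gives d = (1.960 + 0.842) × √(2/39) = 0.634.

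**Inputs.** n = 39 per arm and 1:1 allocation are from the protocol. The PedsQL effect, its SD, the baseline correlation and the cost variance are not given. They are assumed below, over a range.

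**Precision of the denominator, unadjusted.** In SD units, SE = √(2/39) = 0.226 and the 95% half-width is 1.96 × 0.226 = 0.44. With 40 per arm it is also 0.44. For an assumed SD of 10, 15 or 20 points the half-width is 4.4, 6.7 or 8.9 points.

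**Effect of that error on the ICER.** The cost difference is held fixed and the interval is centred on the assumed effect d. P(estimate ≤ 0) = Φ(−d/SE). The ICER limits, as multiples of the point value, are d/upper and d/lower.

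| Assumed d | 95% interval (SD) | P(estimate ≤ 0) | ICER as multiple of point value |
|---|---|---|---|
| 0.2 | −0.24 to 0.64 | 0.19 | unbounded |
| 0.3 | −0.14 to 0.74 | 0.09 | unbounded |
| 0.5 | 0.06 to 0.94 | 0.014 | 0.53 to 8.9 |
| 0.634 | 0.19 to 1.08 | 0.003 | 0.59 to 3.3 |

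**Cost-only range against a joint interval.** Scale both differences to a mean of 1, take them as independent, and let s_c and s_e be their relative SEs. Fieller's limits are (1 ± √(1 − AB))/A, with A = 1 − 1.96²s_e² and B = 1 − 1.96²s_c².

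For d = 0.5 and an assumed s_c = 0.25:
- s_e = 0.226/0.5 = 0.453, so A = 0.212 and B = 0.760.
- The limits are (1 ± 0.916)/0.212, or 0.40 to 9.0.
- Varying cost alone gives 1 ± 1.96 × 0.25, or 0.51 to 1.49. The joint interval is 8.8 times as wide.

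For d = 0.634 with the same s_c, the limits are 0.43 to 3.5, 3.1 times as wide. In the mildest case tried (d = 0.8, s_c = 0.5) the joint interval is 1.45 times as wide. At d = 0.3, A is negative and the interval is unbounded whatever the cost variance.

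**With baseline adjustment.** SE is multiplied by √(1 − ρ²). At an assumed ρ = 0.7, SE = 0.226 × 0.714 = 0.162 and the half-width is 0.317.
- d = 0.3: −0.02 to 0.62, with P(estimate ≤ 0) = 0.03.
- d = 0.5: 0.18 to 0.82, so the ICER runs from 0.5/0.817 = 0.61 to 0.5/0.183 = 2.7 times its point value.

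At ρ = 0.75 the half-width is 1.96 × 0.226 × 0.661 = 0.29, and the interval at d = 0.3 just excludes zero.

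**The case against.** The strongest case against has four parts.

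- **Effect uncertainty is reported elsewhere.** A reader might infer that the plan treats the PedsQL difference as known. It does not: the Data Analysis overview has the variance and P value of mean differences reported for the regressions on the efficacy measures. This stands. The gap is confined to the ICER, into which those figures are not carried.
- **No confidence interval for the ICER is promised.** A reader might infer that the plan offers an invalid interval built by moving one input at a time to its limits. The text says neither. It describes scenario analyses, which may move several inputs together, and with the retail price undecided, price scenarios answer a legitimate question of their own. This stands too. They are the only uncertainty analysis stated for the ratio, however, and they cannot do that job.
- **A fuller analysis plan may hold the detail.** That is possible. But this article is the protocol of the economic evaluation, and it states which uncertainties will be explored and by what means. A stated method that leaves out the denominator is more than a condensed detail, although the list is not called exhaustive.
- **The sizes are assumed.** A reader might infer that the reported range must be far too narrow or the true interval unbounded. The documents give no PedsQL effect, SD, baseline correlation or cost variance, so neither statement holds unconditionally. At larger effects, or with strong baseline adjustment, the interval is bounded and the loss is smaller.

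**Conclusion.** The concern holds for the ICER. Followed as written, the plan yields ICERs that reflect uncertainty in price, costs and TU but not in the PedsQL difference or in the correlation of cost with effect.

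The firm figure is the unadjusted half-width of about 0.44 SD at 39 completers per arm, which needs only the planned number and equal SDs. The rest is conditional: an unbounded ICER interval at assumed effects of 0.2 to 0.3 SD, about 0.5 to 9 times the point value at 0.5 SD, and narrower limits with baseline adjustment. The joint intervals also assume independent cost and effect differences and cost SEs that are not in the protocol.

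The estimates of incremental cost and incremental effect are not themselves affected. What is affected is how much confidence a reader can place in their ratio.

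**What to change.** Amend the Reference Case CEA and Sensitivity Analysis sections as follows.

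1. Use a nonparametric bootstrap that resamples families within arm, and within diagnosis stratum where numbers allow (the protocol expects few CP and FASD participants). Keep each family's cost and PedsQL values together, and combine the bootstrap with the multiple imputation.
2. Report incremental cost and incremental effect, each with a 95% CI, and plot the cost-effectiveness plane.
3. Report net benefit with a 95% CI, or an acceptability curve, over a prespecified range of values per PedsQL point.
4. Give an interval for the ICER only when the effect interval excludes zero.
5. Keep the price and TU scenarios, labelled as deterministic additions.

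The cost is a few lines of text and some computing time. No new data are needed, and the Results section says that the data for the economic evaluation are cleaned and being prepared for analysis. There are two drawbacks. Reported uncertainty will be wider, and a range of values per PedsQL point must be chosen, since the protocol gives none. If no range can be agreed, items 1, 2 and 4 still meet most of the concern.

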### Missing Data

Multiple imputation techniques are used to address missing data. This method works well for longitudinal data and is robust to violations of the nonnormality of the variables analyzed. Participants who do not complete both the baseline and the 8-month follow-up will not be included in the analysis. Where applicable, the measures’ user guides on missing data will be followed. For the PedsQL, the means of completed items in the scale will be imputed when 50% or more of the items are completed [34].

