### Time Horizon

In the BNBD-NDD RCT, data collection occurred at baseline, 4 months, and 8 months. The reference case CEA and secondary CCA will use an 8-month time horizon, focusing on baseline and 8-month data; 8-month data are used to best capture the longer term costs and effects.

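### The exclusion of families without 8-month follow-up stops multiple imputation from addressing dropout, so on the plan's 50% figure the ICER would rest on about half of those randomised

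*Protocol article*

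**What the plan says.** The Missing Data section of the protocol article opens with "Multiple imputation techniques are used to address missing data" and commends the method for longitudinal data. It then restricts the analysis set: "Participants who do not complete both the baseline and the 8-month follow-up will not be included in the analysis". For gaps within a questionnaire it adds a separate rule: "For the PedsQL, the means of completed items in the scale will be imputed when 50% or more of the items are completed".

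The Time Horizon section fixes which waves matter: "The reference case CEA and secondary CCA will use an 8-month time horizon, focusing on baseline and 8-month data". Data were also collected at 4 months.

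The Sample Size Calculation section gives the loss that the trial was planned around, "the anticipated postenrollment dropout rate of 50% from a previous BNBD RCT", and an enrolment target of 160.

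The Sensitivity Analysis section varies estimated costs, reported health care usage, the price of the programme and the confidence limits for treatment utilization. It lists nothing on missing outcomes or dropout.

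**The concern.** The largest expected source of missing data is families who do not return at 8 months. Multiple imputation is the tool named for missing data, yet the exclusion rule takes those families out first. The reference case then compares families who stayed with families who stayed, not the groups as randomised.

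That matters for three reasons.

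- Randomisation protects a comparison of everyone allocated. It does not protect a comparison of the half who remain. Participants knew their allocation, and the usual care group could use the programme only after finishing the 8-month assessments, so the reasons for staying may differ between arms.
- The denominator of the ICER is the between-group difference in PedsQL total score. Any bias in that difference passes straight into the headline result.
- The Perspective section says that the evaluation is meant to inform families about a direct-to-user product. A result confined to those who remain under observation answers a narrower question than the one a prospective user asks.

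**Working it through.** **Step 1: the plan's own figure.** The inputs come from the Sample Size Calculation section: 39 completers per group, 50% dropout, target 160.

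- Completers needed: 2 × 39 = 78.
- Enrolment needed: 78 / (1 − 0.5) = 156, against 160 stated. The target reproduces to within 3%, so the 50% is used as the proportion of enrolled participants lost.

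**Step 2: how many the rule removes.**

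- Excluded: 160 × 0.5 = 80.
- Retained: 160 − 80 = 80, or 78 if only the required number remain.
- Analysed if all randomised participants are kept and 8-month data are imputed: 160.

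**Step 3: what imputation still has to do.** The rule requires the same two waves on which the analysis focuses, so a family with no 8-month visit is never imputed. PedsQL scales that are at least half complete are handled by the mean of the completed items. Multiple imputation is left with scales less than half complete, cost items and covariates such as household income, all among families who completed both visits.

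**Step 4: can the direction of bias be found?** Let d be the proportion lost in an arm, and g the amount, in SD of PedsQL, by which completers in that arm do better than those lost. The all-randomised mean is the completer mean minus d × g, so the completer mean is too high by d × g. For the between-group difference (subscript T for BNBD-NDD, C for usual care):

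bias = d_T × g_T − d_C × g_C

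The article gives no value of d by arm and no value of g. The values below are assumptions, chosen only to show the range:

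| d_T | d_C | g_T | g_C | Bias (SD) |
|---|---|---|---|---|
| 0.5 | 0.5 | 0.3 | 0.3 | 0.15 − 0.15 = 0 |
| 0.5 | 0.5 | 0.3 | 0 | 0.15 − 0 = +0.15 |
| 0.5 | 0.5 | 0 | 0.3 | 0 − 0.15 = −0.15 |
| 0.6 | 0.4 | 0.3 | 0.3 | 0.18 − 0.12 = +0.06 |
| 0.4 | 0.6 | 0.3 | 0.3 | 0.12 − 0.18 = −0.06 |

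**Step 5: effect on the ICER.** Assume a true effect E of 0.3 SD and an incremental cost that does not change. The completers' ICER is then E / (E + bias) times the true one:

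- bias +0.15: 0.3 / 0.45 = 0.67
- bias +0.06: 0.3 / 0.36 = 0.83
- bias 0: 1.0
- bias −0.06: 0.3 / 0.24 = 1.25
- bias −0.15: 0.3 / 0.15 = 2.0

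The sign depends on inputs that the article does not contain.

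**The case against.** The sponsor could fairly answer on several counts.

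- *The sentences do not contradict each other.* Imputation can still fill gaps among completers. The Outcomes for Economic Evaluation section itself expects uneven reporting of school functioning, and costs and income may be incomplete too. This stands. The fault is that the rule keeps imputation away from loss to follow-up, not that it leaves imputation nothing to do.
- *The 50% is a planning figure from a previous trial.* This also stands. Data collection has ended and the actual loss is not reported. The count of about 80 is what the plan itself anticipated, not what happened.
- *The 4-month data may be used as predictors.* The Time Horizon section speaks of focus and does not rule out 4-month measures in an imputation model. The choice of predictors may properly sit in an analysis plan. But predictors cannot help families who have already been excluded.

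A reader might go further and infer that the rule favours BNBD-NDD, because parents who find the programme unhelpful would be the ones to leave. The documents do not support that. Usual care families who are doing badly may leave as well, which works the other way. Intervention families may stop responding because the child improved. Equally selective loss in both arms gives no bias in the difference.

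A reader might also assume that those lost gain between none and half of the completers' benefit, and conclude that the ICER is understated 2.0 to 1.33 times (1 / 0.5 and 1 / 0.75). That treats a missed 8-month assessment as not using the programme. The recommended completion time is 5 to 10 weeks, so a family can finish every session and still miss the questionnaire. The factor also needs incremental cost to be the same in those lost and those retained, which nothing in the article establishes.

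**Conclusion.** The concern holds in this form: a stated exclusion rule prevents the stated method from dealing with the main expected source of missing data. If the planned 50% loss occurred, the ICER would rest on about 80 of 160 randomised families in an unblinded trial, and none of the listed sensitivity analyses would reveal the effect of that loss. The count depends on the planning figure.

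The direction and size of any bias are unknown. The span of 0.67 to 2.0 times shows only what modest, assumed differences between those lost and those retained could do to the ratio. It is not an estimate for this trial. The point is worth correcting before analysis because it affects the reference case result. The Results section says that the economic data were still being prepared for analysis.

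**What to change.** Delete the sentence that excludes participants without both visits, and replace it with a statement along these lines:

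- The reference case includes all randomised participants, analysed as allocated.
- Missing 8-month PedsQL scores and costs are multiply imputed separately by arm. Predictors are the baseline data, whatever 4-month measures were collected, the diagnosis stratum and, in the intervention arm, programme usage from the platform.
- The completers-only analysis is reported as a sensitivity analysis.
- One missing-not-at-random scenario is added, for example with intervention families lost to follow-up given outcomes like those of usual care.

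The article does not say whether PedsQL and treatment utilization were recorded at 4 months, so the wording should not presume it. Reporting the number lost in each arm would let readers judge how much depends on the imputation.

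The cost is a wording change and modest extra analysis, with no new data collection. The main analysis would rest on a missing-at-random assumption, which the added scenario tests, and intervals may be wider.

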### Discount Rate

As all costs and outcomes assessed are within 1 year, a discount rate will not be applied [25].

### Ethics Approval

All study participants provided informed consent to participate in the BNBD-NDD RCT. Ethical approval for the BNBD-NDD trial (REB-1020681) was granted by the IWK Health Centre Research Ethics Board and the associated economic evaluation by the IWK REB and the University of Calgary Conjoint Health Research Ethics Board (REB22-0694). This study complies with all applicable standards and procedures of the IWK REB, the Personal Health Information Act, the Personal Information International Disclosure Protection Act, and the Tri-Council Policy Statement: Ethical Conduct for Research Involving Humans.

## Results

The BNBD-NDD RCT data collection started in June 2019 and ended in April 2022. Research funding was obtained from the Kids Brain Health Network in 2015. Ethics were approved by the IWK Ethics Board and Conjoint Health Research Ethics Board in January 2019 and June 2022, respectively. The data examining the primary outcomes of this RCT are currently being analyzed. The relevant data for the economic evaluation have been cleaned and are being prepared for analysis.

## Discussion

In this paper, we have described an economic evaluation protocol for the BNBD-NDD eHealth intervention, which aims to improve insomnia in children with NDDs. The economic evaluation will identify, measure, and value the costs and outcomes of BNBD-NDD compared to usual care. The reference case CEA will assess the costs and QoL of the children, and the CCA will examine measures beyond QoL for the children and their caregivers.

The prevalence of sleep disorders has been observed to be higher in children with NDDs relative to TD children [40]. BNBD-NDD has the potential to deliver an evidence-based and cost-effective insomnia intervention to children with NDDs, which is critically important given the lack of available treatments. The eHealth delivery system may also overcome some existing barriers to treatment access. If cost-effective, this program can improve sleep outcomes and positively affect the well-being of children with NDDs and their caregivers. To our knowledge, BNBD-NDD is the first eHealth insomnia intervention for children with NDD. No published reports have evaluated internet-based interventions for insomnia in preschool- and school-aged children; 1 study has reported an effective internet intervention for sleep disturbances in infants and toddlers [41].

Some limitations of this study are the uncertainties with cost estimates, the parental-reported measures on behalf of the children, the recall bias of their children’s 12-month service usage, and the lack of objective outcome data. With family and societal payer perspectives, the breadth of the costing analysis is limited by the collected cost data in the RCT and thus likely to be an underestimation of real-world costs. While the CCA provides a wider scope of relevant outcomes and costs for decision makers, the interpretation of the results may be prone to subjective bias [24]. The BNBD intervention would benefit from real-world evidence to evaluate its effectiveness and also explore its applicability to children with other medical conditions.

Despite a direct-to-user approach for the intervention, the economic evaluation can stimulate conversations with relevant stakeholders, better understand the efficacy of web-based alternatives, and provide evidence to support potential public payer funding initiatives. Dialogue on the integration of eHealth interventions in the delivery of care in the health system is another area for future examination. The findings of this study will provide users and other stakeholders with a holistic picture of the costs and impacts of BNBD-NDD and play a role in informed decision-making for resource allocation.

